###### Barriers to participation:

Participants are asked “To help us understand barriers to participation, if you missed a session, please indicate the reason why you were unable to attend (e.g., schedule conflict, transportation, didn’t feel up to it, forgot).”

##### Clinical

To measure *dynamic balance function*, we collect Mini Balance Evaluation System Test (MiniBEST), which evaluates sensory organization, anticipatory and reactive postural control, and dynamic gait indices (75) was found to discriminate BC survivors from controls in at least one prior study (64), and has been recommended for use in studies of neuropathy (18). The subtasks enable calculation of postural control variables of interest for predicting fall risk.

To measure *walking endurance*, we collect the 6-minute walk test (6mwt), which quantifies the distance an individual can walk within 6 minutes, where shorter distances correlate with poorer function including among survivors with CIN (76). Meta-analysis of 6mwt results among adults with pathology or fear of falling indicate that 14.0–30.5 m represents the minimum clinically-important difference (MCID) for improvement in this measure (77). Among BC survivors, a separate meta-analysis found that BC survivors cover less distance as compared to individuals living without cancer (78). The 6mwt is performed in a designated space within each site’s oncology clinic, in a quiet area without distractions. Participants walk in a loop with the following configuration: a straight distance of 19.8 m minimum marked by tape on the floor that participants turn around to their left; participants are cued to walk straight between tape marks and to turn comfortably at the end of each straightaway at the fastest pace they feel they can maintain for 6 min, resting as needed in a standing position before continuing.

As a further measure of CIN and sensation, we will use the *Total Neuropathy Score (TNS) - Revised* (79) (TNSr) with the “sense of touch” section added per Streckmann et al. (2024) (80). This tool measures peripheral nerve impairments in the upper and lower extremities by evaluating symptoms, sensation, and deep tendon reflexes. In the shortened and revised TNS, subjective sensory symptom presence of tingling, numbness, and pain are evaluated in both the upper and lower extremity. Sensation of vibration is evaluated with a Rydel-Seiffert 128 Hz tuning fork on the bony processes of the upper and lower extremities from distal to proximal, while perception of touch is evaluated by stroking the upper and lower extremities. Finally, deep tendon reflexes of the upper and lower extremities are assessed from distal to proximal.

*Upper extremity (UE) function* will be measured using the back scratch item from the Senior Fitness Test (81). Grip strength will be measured using a standardized digital hand grip dynamometer (Jamar 3-piece Dynamometer, Fabrication Enterprises, Elmsford, NY). In the rehabilitation of individuals with neuropathy, grip strength has shown to be an important clinical outcome in assessing upper extremity impairment and is an important predictor of functional status, muscular endurance, and overall strength (82–84). Participants will be seated comfortably with their elbow flexed at 90 degrees, forearm in a neutral position, and wrist in slight extension. After a demonstration and one practice attempt, each participant will perform three maximal grip efforts with a rest period of 10 seconds between trials to prevent fatigue. The maximum of the 3 trials will be used for analysis.

###### Occupational performance:

The Canadian Occupational Performance Measure (COPM) (85) will be administered through a collaborative process with each participant to identify the patient-reported 5 most important occupations related to self-care, leisure, or productivity. In a semi-structured interview with the study therapist, participants will rate their current performance and satisfaction with performance on each activity using an ordinal scale ranging from 1 to 10 points, with higher scores indicating better scores. These assessments will be conducted at baseline (pre-intervention) and repeated at the conclusion of the intervention (post-intervention) to gauge any changes in functional performance and perceived satisfaction. A change of 2 points is considered the threshold for a clinically meaningful change (85). This individualized, client-centered approach of this COPM instrument allows for precise measurement of intervention outcomes, ensuring that improvements in daily functioning are accurately captured and meaningful to the participants (86–88).

##### Biomechanical

Measures of *walking variability and stability* have been found indicative of mild cognitive impairment (89), age (90), fall risk (91–93), and neuropathy (94,95) regardless of age or type of cancer (96) including specifically in BC (16,94,97). Gait stability measures will be collected using inertial measurement units (IMUs) (Trigno Centro, Delsys, Natick, MA) affixed to the foot, leg, thigh, pelvis, and/or lower cervical spine during while participants perform the 6mwt (98), where foot IMU sensors will detect heel strike and toe off events within the gait cycle. The non-linear measures of local dynamic stability (99–102) and recurrent quantification analysis (RQA) (103) will also be analyzed. An IMU sensor placed on the upper torso (C7 vertebral spine) will collect gyroscopic data to detect bouts of steady-state walking behavior along a straight path within the 6mwt. Steady-state bouts of walking that are longer than 4 strides (101,104) will be used to calculate non-linear measures of gait stability. From this, mean Lyapanov exponent and RQA measures will be calculated over the course of the 6mwt. From the steady-state bouts, the coefficient of variation (CV) will also be calculated for step length, gait speed, and other measures of variability previously found sensitive to health status (91,92,105).

We measure *postural control* through center of pressure (COP) data collected in accordance with our group’s previous studies of balance deficits (46,47,50). Data are recorded on a portable balance plate (Bertec Corporation, Columbus, OH) at while participants stand on the plate quietly with their eyes closed (QEC). The data are captured using custom software written in LabVIEW (National Instruments, Austin, TX) at a sampling frequency of 1000 Hz and consist of one channel of vertical force data (Fz) and two channels of moment data (Mx, My) over time.

Additionally, we complete the QEC measure while listening to music (QECm) to examine the relationship between music listening and postural control over the course of the intervention, as it has been shown that postural control improved amongst healthy college-aged individuals after listening to music (37). We follow the same protocol listed in our group’s previous work, where a participant completes a QEC posture while listening to the musical composition “La Cumparsita” (46).

From the QEC and QECm data, we calculate the COP time series for the 30-s duration of QEC condition performance. We then calculate the measures of future fall risk from the two tasks: COP variability in resultant and medial– lateral planes (RMSr, RMSml), medial-lateral sway velocity (COPv), and 95% ellipse area (COPa) for the 30-s duration per Prieto et al., (1996) (51) well as sample entropy using the increment method of calculation (SEI) (52).

*Co-contraction index (CCI)* is the ratio of the muscle activity produced in the agonist versus the antagonist muscles of the leg, measured via electromyography (EMG), which can provide unique insights into neuropathy effects (106). For this protocol, we measure signals in the tibialis anterior, lateral gastrocnemius, and soleus muscles during performance of the 6mwt, QEC, and QECm tasks.

### Exploratory measures

#### Blood-based biomarkers

Blood sample data collections will occur at baseline, after 4 weeks of usual care for members of the CON group, and after 8 weeks of intervention for members of the EXP group. Blood sample collections will occur in the same facilities mentioned in the *Study Setting* section, during scheduled clinical or research appointments. Blood will be drawn in two 6 mL EDTA tubes at the timepoints described previously. Best practice regarding collection and centrifugation will be followed to extract the plasma layer and store aliquots (107). All cryovials containing plasma will be labeled and stored in a −80°C freezer, accessible to laboratory personnel only. Aliquots from each timepoint per participant ID will be shipped to Yale facilities for further processing on an annual basis.

Blood-based biomarkers of interest include targeted indices linked to breast cancer (7,108), neurorecovery (109–111), and neurotoxicity/trauma (7,112). Panels of markers will be measured in plasma. We will investigate a battery of biomarkers using singleplex assays. We list these in order of priority for analysis below in the even that unexpected funding changes impact biomarker analysis budget:
Neurofilament light (NfL) and glial fibrillary acidic protein (GFAP) (Benashley et al., 2022; Burgess et al., 2022; Rodwin et al., 2022).Interleukin-6 (IL-6), IL-10, brain-derived neurotropic factor (BDNF) (7,114), tumor necrosis factor α (TNF-α) (109,111).Other cytokine and inflammatory biomarkers associated with neurotoxicity including but not limited to: IL-7, IL-8, IL-9, interferon gamma (IFN-γ), interferon induced protein 10 (IP-10; CXCL-10), macrophage derived chemokine (MDC), monocyte chemoattractant protein 1 (MCP1; CCL-2), transforming growth factor-α (TGF-α), serum amyloid protein (SAA), endothelial markers (ICAM-1, VCAM-1) (108,109).

At the baseline, after 4 weeks for the CON group, and after 8 weeks for the EXP group, we will measure NfL, a neuronal cytoskeletal protein that has indicated axonal damage in animal CIN models and survivors (7). NfL serum concentration will be assessed by ultrasensitive single molecule array (Simoa NF-Light^®^ assay, Quanterix, Billerica, MA).

We will investigate synaptic plasticity through via BDNF and GFAP, sampled at baseline, after 4 weeks for the CON group, and after 8 weeks for the EXP group. BDNF levels will be analyzed at the Yale facility, while GFAP levels will be assessed by the Quanterix laboratory (Quanterix, Billerica, MA).

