**Methods:**

In a multi-center, prospective, randomized controlled clinical trial, participants are randomly assigned (1:1 ratio) to the Tango experimental or the SOC active control arms. Primary outcomes are measured from baseline to after 4 weeks of intervention in patient-reported outcomes (PROs) of sensation and dual-task function. Secondary outcomes include additional PROs, such as fatigue, and clinical measures of interest after 4 and 8 weeks of intervention and 1 month following intervention completion. Exploratory measures include postural control, gait stability, cognitive load, and blood-based biomarker concentrations. Linear mixed models will be used to model changes in PROs and function. The primary estimand will be the difference in mean change in primary outcomes from baseline to week 4 between treatment groups.

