### Statistical analysis

All outcome analyses will be performed on an intent-to-treat basis, and all hypothesis tests will be two-sided and at the 5% significance level or 95% confidence level. Longitudinal linear mixed models will be used to model changes in PROs and dual-task function. Fixed effects will be included for condition, session number within condition, baseline outcome measure, age, diabetes status, physical fitness activity (defined by weekly duration and metabolic equivalents), and number of previous chemotherapy lines. Random effects for subjects and study center will be used to account for within-subject and within-center correlation, and covariance estimated by restricted maximum likelihood. Exploratory Aim 3 will be assessed via causal mediation analysis using marginal structural models. The primary estimand will be the contrast representing the difference in mean change in outcome measure from baseline to week 4 (end of randomized treatment comparison) between treatment groups.

While we expect balance between groups due to randomization, we will adjust for potential confounders including age, body mass index, concurrent medications, and other variables if an imbalance between groups occurs by chance. Pearson’s *R* will be calculated to correlate PROs, functional outcomes, biomechanical outcomes, brain activity, and biomarker outcomes. We use a longitudinal mixed effect model to analyze all outcomes and do not impute missing outcomes. Subjects will be analyzed in the group to which they were randomized regardless of compliance with the assigned intervention. We will evaluate the effect of the number of intervention sessions completed on outcomes.

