## Figures and Tables

**Figure 1 F1:**
[figure not shown]
Flow chart of study design from screening through the follow-up (f/u) period with assessments indicated throughout. Postural control data will be taken at each Tango session in addition to all assessment periods. Each assessment timepoint may contain 1) clinical measures: PROs, dual-task function, and upper extremity function; 2) biomechanical measures: postural control and gait stability; and 3) exploratory measures: biomarker and EEG sampling. For more detailed information, refer to tables 1 & 2. Processing of data will happen after the conclusion of the follow-up period per participant. Analysis of the primary outcome measures will be conducted after all data has been collected.

**Table 1 T1:** SPIRIT report of intervention effect outcome measures for EXP group.

	Study Period						
	Enrollment		Allocation	Post-Allocation			
Timepoints	3 + months post-last taxane exposure	Baseline	0	EXP 4 weeks (Tango midpoint)	EXP 8 weeks (Tango end)	EXP 12 weeks (1-month follow up)	6-month follow up period, assessed weekly
ENROLLMENT:							
Eligibility screen	x						
Informed consent	x						
Allocation			x				
ASSESSMENTS:							
Adverse events (including falls)		x^†^		x	x	x	x
Neuropathy (primary outcome Aim 1)		x^†^		x	x	x	x
TUG-Cog (primary outcome Aim 2)		x		x	x	x	
CTCAE		x^†^		x	x	x	
Pain		x^†^		x	x	x	
Fatigue		x^†^		x	x	x	
GAD-2		x		x	x	x	
PHQ-2		x		x	x	x	
SF-36		x		x	x	x	
Satisfaction with intervention				x	x		
Activity outside of study tracking		x^†^		x	x	x	x
Intrinsic motivation				x	x		
Postural control during silence (QEC)		x^†^		x	x	x	
Postural control during music listening (QECm)		x^†^		x	x	x	
TUG		x		x	x	x	
TNSr+		x		x	x	x	
MiniBEST		x			x		
6mwt (EMG, IMUs)		x			x		
Upper extremity function		x		x	x	x	
Goal attainment (COPM)		x			x	x	
Blood-based biomarkers		x			x		
Cognitive load (EEG)		x		x	x	x	

† indicates a measure was repeated 3 times

**Table 2 T2:** SPIRIT report of intervention effect outcome measures for CON group.

	Study Period							
	Enrollment		Allocation	Post-Allocation				
Timepoints	3 + months post-last taxane exposure	Baseline	0	CON 4 weeks (post-SOC)	CON 8 weeks (Tango midpoint)	CON 12 weeks (Tango end)	CON 16 weeks (1-month follow up)	6-month follow-up period, assessed weekly
ENROLLMENT:								
Eligibility screen	x							
Informed consent	x							
Allocation			x					
ASSESSMENTS:								
Adverse events (including falls)		x^†^		x	x	x	x	x

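### Blood biomarkers, MiniBEST and the 6-minute walk share no post-baseline week between arms, so they give no time-matched Tango-versus-SOC contrast, and the biomarkers cannot support the Aim 3 mediation analysis

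*Protocol article*

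**What the plan says.** Under Blood-based biomarkers, the protocol article schedules sampling at baseline and then "after 4 weeks of usual care for members of the CON group, and after 8 weeks of intervention for members of the EXP group". The same split is repeated for NfL ("At the baseline, after 4 weeks for the CON group, and after 8 weeks for the EXP group, we will measure NfL") and for BDNF and GFAP ("sampled at baseline, after 4 weeks for the CON group, and after 8 weeks for the EXP group").

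The schedules are Table 1 ("SPIRIT report of intervention effect outcome measures for EXP group") and Table 2 ("SPIRIT report of intervention effect outcome measures for CON group"). They match the text on blood and show a similar split for MiniBEST and 6mwt. COPM is absent at week 4 in EXP but present in CON.

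Statistical analysis defines the primary estimand as the between-group difference in mean change to week 4, which it describes as the close of the randomised comparison. It applies a longitudinal mixed model to all outcomes and adds: "Exploratory Aim 3 will be assessed via causal mediation analysis using marginal structural models". Study Design presents the biomarkers as possible mediators of sensation and function. The section on the control intervention lets CON participants start Tango straight after the week-4 assessment. Objectives ties the exploratory hypothesis to 8 weeks of Tango.

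**The concern.** A between-arm difference can be read as Tango versus SOC only if both arms are measured at the same time since randomisation and CON is still on SOC. For blood, MiniBEST and 6mwt no visit meets both conditions. The 6mwt also carries the IMU gait-stability data and part of the EMG data.

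Mediation needs more: a mediator measured in both arms, no later than the outcome it is meant to explain. If the analysis goes ahead on this schedule, a change due to natural course over four further weeks could be reported as an effect of Tango, or as a pathway through which Tango works. An analysis plan cannot repair this, because it cannot supply a sample that was never drawn.

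**Working it through.** **Step 1. Schedule, read cell by cell from Tables 1 and 2 (post-baseline weeks).**

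| Measure | EXP | CON | Shared weeks |
|---|---|---|---|
| Blood | 8 | 4 | none |
| MiniBEST | 8 | 4, 12 | none |
| 6mwt (IMU, EMG) | 8 | 4, 12 | none |
| COPM | 8, 12 | 4, 8, 12, 16 | 8, 12 |
| EEG | 4, 8, 12 | 4, 8, 12, 16 | 4, 8, 12 |

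None of the first four measures has an EXP value at week 4. The two shared COPM weeks fall after the CON crossover opens, so they compare immediate with delayed Tango. EEG, the other Aim 3 measure, is taken at week 4 in both arms.

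**Step 2. The other possible pairing.** EXP week 8 and CON week 12 for MiniBEST and 6mwt both follow 8 weeks of Tango, for CON participants who cross over. They are matched on exposure but not on time since randomisation (8 versus 12 weeks), and neither side is SOC.

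**Step 3. Mediation under each outcome week.** Statistical analysis does not name the week.
- Week-4 outcome: the EXP biomarker is drawn 8 − 4 = 4 weeks after the outcome it should explain.
- Week-8 outcome: CON has no week-8 sample, and its participants may already be on Tango.

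**Step 4. Sample size behind the illustration.** Power calculations gives 50 completers per arm and about 80% power. The standard error of a difference in SD units is √(2/50) = 0.20.
- Aim 1: SD = √((2.5² + 1.9²)/2) = 2.220, and 1.25/(2.220 × 0.20) = 2.81. Power = Φ(2.81 − 1.96), about 80.4%.
- Aim 2: 0.56/0.20 = 2.80. Power = Φ(2.80 − 1.96), about 80.0%.

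The stated power reproduces, so 50 per arm is used below.

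**Step 5. Illustration of the time mismatch.** Assume no Tango effect and a drift common to both arms, expressed in SDs of the quantity compared. The bias of EXP week 8 minus CON week 4 is b = 4 × weekly drift. The two-sided rejection rate is 1 − Φ(1.96 − b/0.20) + Φ(−1.96 − b/0.20).

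| Assumed drift per week | Bias b | b / SE | False-positive rate |
|---|---|---|---|
| 0.02 SD | 0.08 SD | 0.4 | about 7% |
| 0.05 SD | 0.20 SD | 1.0 | about 17% |
| 0.10 SD | 0.40 SD | 2.0 | about 52% |

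The protocol gives no drift for any of these measures, so the rates show how sensitive the contrast is. They do not estimate what will happen.

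**The case against.** The best defence is that week 8 is deliberate. Objectives expects exploratory measures to change with 8 weeks of Tango, and the EXP sample at the end of the programme serves that hypothesis. This stands, and it is why the week-8 EXP values should be kept. It justifies within-EXP change, but not a contrast with SOC and not mediation.

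Several stronger readings are tempting, and the document does not support them:
- **That no randomised comparison exists.** The arms remain randomised. What is missing is a time-matched contrast with SOC, and COPM can still be compared by arm at weeks 8 and 12.
- **That every between-arm contrast sets 8 weeks against 4.** This is true for blood only. MiniBEST and 6mwt also have the CON week-12 value.
- **That the abstract's schedule is broken.** It says that secondary outcomes include "clinical measures of interest after 4 and 8 weeks of intervention and 1 month following intervention completion", which does not promise every measure at every visit. EXP has TUG, TNSr and upper extremity function at week 4.
- **That practice effects bias the contrast.** MiniBEST and 6mwt are not marked as repeated at baseline, so EXP week 8 and CON week 4 are each the second administration. The difference is elapsed time.
- **That all EMG data are affected.** The biomechanical section also records EMG during quiet standing with and without music, and both tasks are scheduled at week 4 in both arms.
- **That Aim 3 fails as a whole.** Its EEG part has week-4 data in both arms.

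It is also fair to say that these measures are secondary or exploratory and that no confirmatory claim rests on them. That lowers the severity but does not remove the point.

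**Conclusion.** The point holds for blood biomarkers, MiniBEST and 6mwt, including the gait and EMG data recorded during the walk. They have no post-baseline week in common, and so no time-matched Tango-versus-SOC contrast. COPM is a separate, milder case: its shared weeks answer a different question. The planned causal mediation analysis cannot be validly run with the blood biomarkers, whether the outcome is at week 4 or week 8.

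These conclusions rest on the schedule alone and need no assumption. Only the size of the possible bias does: with an assumed common drift of 0.08 to 0.40 SD over four weeks and 50 per arm, the false-positive rate runs from about 7% to about 52%, against a nominal 5%. Severity is low to moderate. Both primary comparisons, on sensation and TUG-Cog, have week-4 data in both arms and are unaffected.

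**What to change.** Keep the week-8 EXP measurements and change what is claimed from them:
- State that blood biomarkers, MiniBEST and 6mwt are reported as within-arm change and are not tested between arms as Tango versus SOC.
- Label any COPM comparison at weeks 8 and 12 as immediate versus delayed Tango.
- Limit the Aim 3 mediation analysis to candidate mediators that both arms have at week 4 (EEG, postural control), and name the outcome week. These are measured at the same assessment point as the week-4 outcome, so the ordering of mediator and outcome should be stated as an assumption.

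This costs wording only, with no extra visit, draw or test. The price is that the biomarker mediation claim is given up.

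If the sponsor values that claim more than the 8-week EXP biomarker value, the alternative is to move the EXP blood draw to the existing week-4 visit. The number of draws stays the same, but the 8-week change in Objectives could then no longer be tested for biomarkers in EXP. Trial status expects enrolment to run until December 2028, so either change made now would still be useful.

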#### Cognitive load

Brain activity will be collected via electroencephalography (EEG) and occur at baseline, after 4 weeks of SOC or INT, and after 8 weeks of intervention. EEG data collection will occur in the same facilities mentioned in the *Study Setting* section, using a mobile EEG system (eego, ANT Neuro, Netherlands) with 24-channels (waveguard net, ANT Neuro, Netherlands), sampling at a frequency of 2048 Hz. EEG signal processing and analysis will follow Crasta et al. (2018) (115) using BV Analyzer (Brain Vision LLC, Garner, NC) to extract mean activity per frequency band, phase synchrony, and event-related potentials.

The protocol to assess cognitive load follows that of [name] et el., 2024 (17). EEG signals were collected during the performance of the following postural and motor-cognitive tasks. Conditions listed in Table 4 below are completed by each participant while standing with their shoes off, feet 7 cm apart from the inside of their feet, hands to their side, and facing comfortably straight ahead. Participants will be guarded by trained research staff during standing tasks and will get a break at the halfway mark of each task. Each task lasts for 3 minutes. Auditory stimuli will be presented through ER-3A-inserted earphones (Etymotic Research, Elk Grove Village, IL) via a custom-made program in PsychoPy (Open Science Tools, Nottingham, England).

For the visual and auditory oddball, each stimulus is presented for 500 ms with a random inter-stimulus interval from 500 ms to 1 second. A total of 100 stimuli are presented (80 standard and 20 oddball).

